### Assessment of outcomes

#### Asthma control

Asthma Control will be assessed by using the Asthma Control Test (ACT) [30, 33]. The ACT consists of five items that assess (1) activity limitation, (2) daytime shortness of breath, (3) awaking due to asthma symptoms, (4) needed puffs of reliever medication and (5) a global judgment of asthma control. All items refer to the last 4 weeks. They are scaled from 1 to 5. The sum of scores indicates asthma control. An ACT score of 20 – 25 indicates controlled asthma and of <20 indicates uncontrolled asthma. A minimal important difference about 3 was identified [34].

#### Health related quality of life

Asthma specific HRQoL will be assessed by both, the Saint George’s Respiratory Questionnaire (SGRQ) [35] and the standardized version of the Asthma Quality of Life Questionnaire (AQLQ) [36]. The SGRQ uses 50 items to capture the three domains *Symptoms*, *Activity* and *Impacts* as well as a *Total* scale. All scales are computed by weighted sums of the respective items. The scores range from 0 (no impairment) to 100 (maximum impairment). A minimal important difference (MID) of 4 is established for COPD, a MID for asthma has not been reported up to now. The standardized version Asthma Quality of Life Questionnaire (AQLQ) contains 32 questions to capture the four domains *Symptoms*, *Activity limitation*, *Emotional function* and *Environmental stimuli* to measure the functional problems that are most troublesome to adults with asthma. The survey period covers the past 2 weeks. Each question is answered on a 7-point scale (1 = severely impaired - 7 = not impaired at all). The overall AQLQ score is the mean of all 32 responses and the individual domain scores are the means of the items from those domains.

Generic HRQoL of patients is measured using the Euroqol questionnaire (EQ-5D-5L) and the EQ visual analogue scale (VAS). The EQ-5D-5L [37] is a standardized instrument applicable to a wide range of health conditions for use as a measure of health outcome. It is especially suited to cost effectiveness analyses as it can be used to generate quality-adjusted life years [38]. The descriptive system of the EQ-5D-5L comprises five dimensions (mobility, self-care, usual activities, pain/discomfort, anxiety/depression). Each dimension has five levels: no problems, slight problems, moderate problems, severe problems, and extreme problems. A German utility index is currently being developed.

#### Subjective health

Global rating of change (GRC) [39] in subjective health is assessed using a single item that compares current subjective health with subjective health at the beginning of the inpatient rehabilitation. The response scale ranges from -7 (much worse) over 0 (no change) to 7 (much better).

#### Symptoms

Severity of dyspnea, cough, sputum and pain will be assessed with response to seven 11-point numeric rating scales [40]. Scale values range from 0 (no symptoms) to 10 (worst imaginable symptom severity).

#### Fatigue

The Brief Fatigue Inventory (BFI) will be used to measure fatigue. This short questionnaire assesses severity of and impairment from fatigue with ten questions. The subscales and the total score range from 0 to 10, with higher values indicating higher severity/impairment. A German version exists and has been proven reliable and valid [41].

#### Depression and anxiety

The PHQ-9 and the GAD-7 will be used to assess depression [42] and anxiety [43, 44]. All items are scored on a 4-point Likert scale (0 = not at all, 1 = several days; 2 = more than half of the days; 3 = nearly all days). Besides using the sum of scores (which range from 0 to 27 in PHQ and 0 to 21 in GAD-7), we will also classify individuals with values of >10 as indicating a clinically relevant depressive disorder (PHQ-9) or a clinically relevant anxiety disorder (GAD-7).

#### Illness representation

The 9-item Brief-Illness Perception Questionnaire (B-IPQ) [45] will be used to capture 8 aspects of *illness representations* (i.e how illness perceived by the patient: *Consequences*, *Timeline*, *Personal control*, *Treatment control*, *Identity*, *Concern*, *Understanding* and *Emotional response*. Each aspect is assessed by one item, except for *Emotional response*, which is assessed by two items. All items use a 0 to 10 response scale. Furthermore, perceived causes of asthma attacks are assessed via an open-ended response item, which asks for the three most important causal factors of their illness.

#### Subjective self-management

Subjective self-management will be assessed using the *Skill and technique acquisition* scale from the Health Education Impact Questionnaire (heiQ^TM^, [46, 47]). The items are scored on a 4-point response scale (1 = strongly disagree, 2 = disagree, 3 = agree, 4 = strongly agree). The overall score is computed as the unweighted mean of all items, with higher values indicating a higher subjective judgement of self-management.

#### Medication adherence and medication beliefs

Patients will complete the Medication Adherence Report Scale (MARS-D) [48]. This is a 5-item questionnaire with a 5-point response scale (1 = always to 5 = never). The sum of the individual answers can range from 5 to 25 points, with higher values indicating better medication adherence. The 10-item Brief Medication Questionnaire (BMQ) [49] will be used to assess patient’s medications beliefs on two scales. The scale *Necessity* assesses patients’ beliefs about the necessity of prescribed instruments and the scale *Concern* assesses patients’ concerns about prescribed medications. Both scales range from 5 to 25 points with higher values indicating higher belief of necessity/higher concerns.

#### Lung function measurement

Forced expiration in one second (FEV_1_), vital capacity (VC), residual volume (RV) and total specific resistance (SRtot) are determined using spirometry and body plethysmography (MasterLab, CareFusion, Hoechberg, Germany) before and after bronchodilation with a short-acting bronchodilator in accordance with recommendations of the national guidelines [50, 51].

#### Resource use

Resource use will be determined based on answers to the FIMA-Lu questionnaire, a modified Version of the FIMA questionnaire, a German instrument to assess health-related resource use [52]. For direct costs, the number of visits to a general practitioner, specialist care, ambulatory clinics in hospital, physiotherapy, days spent in hospitals and intensive care units and medication administered will be documented. For indirect costs, work absenteeism days will be documented.

#### Exercise Capacity

The 6-MWD will be measured using a track length of 30 m according to the European Respiratory Society/American Thoracic Society technical standards [53]. At T0 and T1 respectively, each patient performs the test twice with an interval of one hour. The best test will be included for analysis.

#### Work ability

Subjective work ability will be assessed by the first item of the Work Ability Index (WAI), the *Work Ability Score* (WAS). It compares current subjective work ability to the lifetime’s best. The 11-point scale ranges from 0 (complete incapacity to work) to 10 (lifetime’s best work ability). The WAS shows high correlations with the overall WAI score [54]. Furthermore, the 4^th^ Item of the WAI is used to assess health-related limitation of current work ability, with values ranging from 1 (total incapacity to work) to 6 (no limitation). In addition, subjective prognosis of employment status will be assessed using the 3- items of the Subjective Prognostic Employment Scale (SPE Scale). The three items assess patient’s belief (a) to remain at work until retirement and (b) whether their health will be permanently jeopardized and (c) whether they are considering applying for a disability pension [55].

#### Sport activity, smoking habits and medication use

Two items will be used to assess sport activity. In Item 1, the patient indicates whether he or she exercises regularly (at least 2 times per week) and in item two the kind of exercise performed (e.g. gym, sports club, lung sport group). Current smoking status (current smoking yes or no) and number of cigarettes per day will be documented. Furthermore, patients’ use of antibiotics or cortisone in the last three months (yes/no; number of uses) will be documented.

#### Socio-demographic data and employment

Information regarding socio-demographic data and employment status will be collected.

##### Data management

Data of all measurement time-points will be collected in the Bad Reichenhall Clinic. Questionnaire data will be entered into Microsoft Excel by two study nurses (independent double data entry by two individuals). A unique ID number will be assigned to each patient and personal data (name, address) will be stored in a completely separate file. The list with assigned ID numbers and personal data will be stored in the Bad Reichenhall Clinic and will not leave the center. Other anonymized data will be sent to the University of Wuerzburg and the Helmholtz Zentrum Munich for further data management and data analyses.

### Statistical methods

Primary and secondary outcomes will be analyzed according to the intention to treat approach [56]. All randomized patients will be included in the analysis. Missing data fulfilling the assumption of missing (completely) at random will be imputed using multiple imputation procedures [57]. In addition, because it may be possible that some patients will not start with the inpatient rehabilitation or decide to drop-out of the study, we will also analyze results based on a “per protocol” approach [58, 59] including only patients remaining in the study until T3.

The analysis of the primary and secondary outcomes at T2/T3 will use analysis of covariance (ANCOVA) with treatment group as a fixed effect and baseline value of the respective outcome as a covariable. Adjusted mean differences and confidence intervals will be reported. In addition, moderating effects [60] of the following baseline variables on the primary outcome will be analyzed: ACT, gender, age, quality of life (assessed via SGRQ Total Score), anxiety (assessed using GAD-7) and depression (assessed using PHQ-7). For all models, statistical model assumptions (linearity, homoscedasticity, normality of residuals) will be tested. If model assumptions are violated, appropriate analysis methods (e.g. robust regression, log-transformation) will be used.

Latent change models will be used for exploratory analyses of the course of the primary and the secondary outcomes in the follow-up longitudinal study [61, 62].

### Economic evaluation

Data regarding resource utilization and work absenteeism will be documented retrospectively by the patient. A self-administrated questionnaire based on the FIMA questionnaire [52] has been developed specifically for patients with pulmonary problems. The monetary valuation of resource use will be based on the valuation rates calculated by Bock et al. [63]. Analysis of cost data will be performed with a model with a gamma distribution and a log-link to account for the skewed distribution of the data [64]. A 95% confidence interval for the cost difference will be estimated based on 1,000 bootstrap replications using the percentile method.

In the longitudinal follow-up study, the annual costs before and after rehabilitation will be compared by paired t-test. Alternatively, bootstrap resampling with 1,000 resamples will be used to compute p-values because cost differences may have a skewed distribution.

All statistical Analysis will be performed using SPSS [65], R [66] & SAS software [67].

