**Methods:**

The EPRA study is a single-center randomized controlled waiting-list trial in the Bad Reichenhall Clinic. Inclusion criteria include a referral diagnosis for uncontrolled asthma, no cognitive impairment and no very severe co-morbidities that indicate significantly greater illness morbidity than asthma alone. In the intervention group (IG), participants will start PR within 4 weeks after randomization; participants of the control group (CG) will start PR 20 weeks after randomization. Data will be assessed at randomization (T0), after 4 weeks (T1; IG: begin of PR), 7 weeks (T2; IG: end of PR), and 20 weeks (T3, CG: begin of PR). The primary outcome is asthma control at T2/T3. Secondary outcomes are health-related quality of life, functional exercise capacity, dyspnea, anxiety, depression, subjective self-management skills, illness perceptions, sick leave and subjective work ability. Outcomes will be analyzed with analysis of covariance, including baseline values of the respective outcomes as covariates. Healthcare costs will be analyzed with a gamma model with a log-link.

A longitudinal follow-up study will generate additional data at 3/6/9/12 months after PR for both IG and CG. Latent change models will be used to analyze the course of the primary and secondary outcomes. Annual cost differences before and after rehabilitation will be compared by paired t-test.

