### Outcomes and measures

The primary outcome is the mean change in AC, assessed by ACT. Secondary outcomes include mean changes in HRQoL, 6-min walk distance (6-MWD) and Sit-to-stand-test, lung function parameters, Eosinophils, dyspnea, depression, anxiety, smoking habits, illness representations, self-management skills, work ability, subjective prognosis of return to work, sick leave, medication beliefs and medication adherence. Measurement instruments for all outcomes and measurement occasions can be found in Table 1. Lung function parameters, 6-MWD, FeNO, and Eosinophils are assessed at the start and the end of the inpatient rehabilitation by staff of the PR. All other outcomes are assessed via questionnaires.

**Table 1 Tab1:** outcome measures

Outcome	measured by/Instrument	T0	T1	T2	T3A (CG)	T3	T4	T5	T6	T7 (CG)	T8 (CG)
Asthma control	Asthma control test (ACT) [29, 30]	X	X	X	X	X	X	X	X	X	X
Lung function, blood gases	FEV1, FEV1/VC, SRtot, VC, RV, PaO2, PaCO2, [50, 51]		IG	IG		CG	CG				
Exercise capacity	6MWT [53]										
Allergy	Total Ig E, specific Ig E-Screening (ImmunoCAP®)		IG	IG		CG	CG				
Asthmatic inflammation	Fractional exhaled nitric oxide (FeNO) [56], Eosinophils		IG	IG		CG	CG				
QoL	Saint George’s Respiratory Questionnaire (SGRQ) [35]	X	X	X	X	X	X	X	X	X	X
QoL	Asthma Quality of Life Questionnaire (AQLQ)] [36]	X	X	X	X	X	X	X	X	X	X
QoL	EQ-5D-5L [37, 38, 57]	X	X	X	X	X	X	X	X	X	X
QoL	Global Rating of Change Scale (GROC-scale) [39]			X	X	X	X	X	X	X	X
Symptoms	Numerical rating scale for dyspnoea, cough, sputum, pain [40]	X	X	X	X		X	X	X	X	X
Dysfunctional breathing	Nijmegen Questionnaire (NQ) [58]	X	X	X	X					X	X
Depression	Patient Health Questionnaire (PHQ) [59]	X	X	X	X		X	X	X	X	X
Anxiety	Generalized Anxiety Disorder Questionnaire (GAD 7) [60]	X	X	X	X		X	X	X	X	X
Fatigue	Brief Fatigue Inventory (BFI) [41]	X	X	X	X						
Illness Perception	Illness Perception Questionnaire (IPQ-R) German Version [45]	X	X	X	X		X	X	X	X	X
Resource Use	FIM-Lu, modification of FIMA [52]	X			X		X	X	X	X	X
Work ability	Work Ability Index (WAI) Items 1 and 4 [61]	X	X	X	X		X	X	X	X	X
SPoRTW	SPE-Scale [55]	X	X	X	X		X	X	X	X	X
Self-management	Health Education Impact Questionnaire (heiQ), Scale “Skill and technique acquisition”	X	X	X	X		X	X	X	X	X
Smoking habits	Questionnaire (developed)	X			X		X	X	X	X	X
Sport behaviour	Questionnaire (developed)	X			X		X	X	X	X	X
Medication beliefs	Brief Medication Questionnaire (BMQ) [62]	X	X	X	X				X	X	X

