Adherence	Medication Adherence Report Scale (MARS) [63]	X	X	X	X				X	X	X
Sick leave	Questionnaire (developed)				IG		X	X	X	X	X

Notes: QoL: Quality of Life; SPoRT: Subjective prognosis of return to work; IG: assessment only in intervention group; CG: assessment only in control grou

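### The between-group cost model names no baseline cost term although resource use is collected at T0 in both arms; adding it would give a more precise cost comparison from data already in hand

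*Protocol article*

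**What the plan says.** For the primary and secondary outcomes, the Statistical methods section prescribes ANCOVA "with treatment group as a fixed effect and baseline value of the respective outcome as a covariable".

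Costs get a separate rule. The abstract says "Healthcare costs will be analyzed with a gamma model with a log-link", directly after the sentence that gives the other outcomes their baseline covariates. The Economic evaluation section repeats the choice: "Analysis of cost data will be performed with a model with a gamma distribution and a log-link to account for the skewed distribution of the" costs. On the interval it then specifies: "A 95% confidence interval for the cost difference will be estimated based on 1,000 bootstrap replications using the percentile method". Neither place names a baseline cost term, and neither writes out the treatment term.

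The baseline data exist. The resource-use row of Table 1 carries an X at T0. The table notes reserve separate marks for single-arm assessments (for example "IG: assessment only in intervention group"), so a plain X covers both arms. T0 is at randomisation, before either group starts rehabilitation.

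Pre-rehabilitation costs are used explicitly only in the longitudinal part, where "the annual costs before and after rehabilitation will be compared by paired t-test".

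**The concern.** The article states its baseline covariate rule for the clinical outcomes in both the abstract and the methods. For costs it goes down to the interval type and the number of bootstrap replications, yet no T0 cost appears. The clinical rule does not clearly reach costs, because healthcare costs are in neither list of secondary outcomes (Study aims; Outcomes and measures). A programmer working from this text alone would probably fit cost on treatment group only.

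Precision is at stake. Patients differ persistently in how much care they use. Without T0 cost, that stable variation stays in the error term and widens the interval. Randomisation is stratified by age only, so the design does not balance earlier costs either. The sample size was set for the ACT, and no power or precision is stated for costs.

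**Working it through.** **The plan's own figure.** The only sample size is for the ACT at T3: d = 0.3, alpha 0.05, power 0.8. A two-sided two-sample t-test needs 175.4, so 176 per arm, or 352 in total. With 30% dropout, 352/0.7 = 502.9, so 503, or 504 for equal arms. Both stated figures reproduce. Neither concerns costs, so no stated figure changes below.

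**Inputs.** m = 176 evaluable per arm, from the Sample size section. The correlation ρ between T0 and follow-up cost is not given; the assumed range is 0.3 to 0.7. Costs are in units of their own SD, taken as equal at both times.

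**What the model gives without a baseline term.** With treatment group alone, a gamma log-link model reproduces the two sample means. The cost difference is then the plain difference in mean cost, with standard error √(2/m) = √(2/176) = 0.107 SD.

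**Effect of adjustment (linear approximation).** The variance is multiplied by 1 − ρ² and the interval width by √(1 − ρ²). The unadjusted sample per arm with the same precision is m/(1 − ρ²).

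| Assumed ρ | Variance cut | Width ratio | Equivalent unadjusted n per arm |
|---|---|---|---|
| 0.3 | 9% | 0.95 | 193 |
| 0.5 | 25% | 0.87 | 235 |
| 0.7 | 49% | 0.71 | 345 |

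The variance cut and the width ratio do not depend on m.

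**Chance imbalance.** The standardised T0 cost difference between arms has SD √(2/176) = 0.107. The part carried into an unadjusted estimate has SD ρ × 0.107 = 0.032, 0.053 and 0.075 for the three correlations. This part is already inside the 0.107 standard error. At ρ = 0.5, 0.053² = 0.0028 is 25% of 0.107² = 0.0114, the same share that adjustment removes.

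**Simulation check.** The linear formula is only approximate for skewed costs, so a gamma log-link model was simulated with no treatment effect, 176 per arm and up to 600 runs per setting. Baseline and follow-up costs shared a lognormal patient effect (SD 0.6 to 0.8) with gamma noise (shape 1 to 3). The covariate was log T0 cost, and the difference was standardised over all patients.

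| Realised ρ | SD of adjusted estimate ÷ unadjusted | Correlation of estimate with T0 imbalance: unadjusted → adjusted |
|---|---|---|
| 0.23 | 0.94 | 0.23 → 0.08 |
| 0.42 | 0.81 | 0.40 → 0.05 |
| 0.59 | 0.74 | 0.57 → 0.02 |

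On a mean cost of about 1,000, average estimates lay between −14 and +11 with and without adjustment, which is near zero. The settings are assumptions, there were no zero costs, and runs in which the model failed to fit were skipped. The check supports the direction and rough size only.

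**The case against.** The strongest objection is that silence is not a decision. The cost sentence fixes a family, a link and an interval method, and omits even the treatment term. A covariate list for a non-primary model is something a condensed article may leave to a fuller plan, which may already name T0 cost. This stands in part: nothing declares an unadjusted model, and any loss depends on running the analysis as written. But the article does give this covariate for its other outcomes, and the change is specific and uses data already collected.

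A reader might infer three stronger things that the documents do not support.

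- **Bias.** A chance difference in T0 costs might seem to be reported as an effect of rehabilitation. Under randomisation the unadjusted contrast is right on average, and its interval already reflects that variability.
- **A known gain in power.** The 80% power and d = 0.3 belong to the ACT. No cost effect, SD or correlation is given, so no power gain for costs can be read from the Sample size section. At ρ = 0.3 the interval narrows by only about 5%.
- **That this contrast is the economic result for payers.** The Discussion promises economic information in general terms. The economic aim in the Study aims section is annual cost before and after rehabilitation, and that paired comparison uses each patient's own earlier costs.

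The recall period of the resource-use questionnaire is also not stated, so how closely T0 cost tracks follow-up cost is unknown. That widens the plausible range of ρ but does not reverse the direction.

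**Conclusion.** The point holds as an efficiency improvement to a non-primary analysis. The article specifies baseline adjustment for its primary and secondary outcomes, names none for costs, and collects the needed baseline in both arms. If the cost model is run as written, the comparison is valid but wider than necessary. Adjusted intervals would be about 5% narrower at an assumed correlation of 0.3, 13% at 0.5 and 29% at 0.7. These figures rest on assumed correlations and a linear approximation; the simulation agrees in direction under its own assumed cost distributions. No stated figure is wrong and no passages contradict each other.

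**What to change.** In the Economic evaluation section, state that:

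- the between-group gamma log-link model contains treatment group and the patient's T0 cost, built from the same questionnaire items and unit costs as the follow-up cost;
- T0 cost enters in a functional form fixed in advance that handles zero costs (adding 1 before taking logs is one option, but it depends on the currency scale);
- the reported result is the standardised adjusted mean cost difference, that is, the average predicted cost with every patient set to the intervention group minus the average with every patient set to the control group;
- this adjusted model is refitted in each of the 1,000 bootstrap replications before the percentile interval is taken;
- missing T0 cost items go through the planned multiple imputation, with the order of imputation and bootstrap stated.

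If a fuller plan already contains the T0 cost term, one sentence saying so is enough. Otherwise the cost is wording and some extra programming, chiefly for combining imputation with the bootstrap. No new data or patients are needed. Fixing the term in advance also removes a later choice between adjusted and unadjusted results.
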